### Statistical Methods

#### Group Comparisons of Primary Endpoints/Hypotheses Testing

If the hypothesis of normal distribution cannot be rejected (Kolmogorov-Smirnov with Lilliefors significance correction, type I error = 10%) and if homoscedasticity exists (Levene's test; type I error = 5%) a parametric analysis of covariance (ANCOVA) will be applied (type I error = 0.833% one-sided). Otherwise, a non-parametric analysis of covariance (rank analysis of covariance according to Quade) will be used (type I error = 0.833% one-sided).

Covariates are

CVLT total trials 1–5/CVLT short delay/CVLT long delay (corresponding variable) at baseline [-]BMI at baseline [kg/m^2^]Age at baseline [years]BDI II at baseline [-]STAI at baseline [-]Fatigue at baseline [yes/no]

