Unfortunately, exercise trials in the context of CRCI have several methodological limitations. The majority of studies (59, 64–66) conducted to date were small in cohorts and time, were not randomized, used a variety of unstandardized objective and subjective cognitive assessments, provided no information on physiological/biological changes, and most essentially did not include imaging techniques to screen for structural correlates in terms of cognitive impairment. Incompliance and lack of adherence in the intervention group are common problems, also when seen to be correlating directly with the median age of study cohort, entity of cancer and especially the type and administration of the exercise intervention (supervised/unsupervised) (67, 68).

Therefore, the ECCO-study bridges the gap between conducted exercise trials by summarizing all findings to CRCI up to this time and integrating them into a randomized controlled trial.

The aim of this study is to investigate the effects of an additional 12 months individualized and supervised HIIT based training program, in contrast to only giving out general physical activity recommendations, on cognition in patients with diagnosed local breast cancer receiving neo-/adjuvant chemotherapy. Secondary aims are to determine the effects of the intervention on physical performance, common cancer related side effects (e.g., fatigue, emotional and physical well-being and QOL), structural changes of the brain, as well as potential underlying biomarkers.

Therefore, we hypothesize, that constant physical activity and additional supervised HIIT in the intervention group results in less cognitive impairment compared to the control group. Hence, the mean (sub)scores “total trial,” “short delay” and “long delay” of the CVLT after 12 months of intervention are hypothesized to be higher in the intervention- than in the control group.

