### Study Endpoints

#### Primary Endpoint

The primary endpoint is the difference from baseline (t_0_) to completion of the exercise intervention (t_2_), in the California Verbal Learning Test (CVLT) mean scores and consists of the three (sub)scores “short-delay,” “long-delay” and “total-trials 1–5” of the CVLT. The CVLT is an instrument commonly used to evaluate the individual verbal learning and memory.

The test consists of two 16-word lists. The word list A is defined as the learning-list; word list B is used to interfere (interference-list). Word list A will be read aloud to the patient 5 times, then list B will read once. After that, the patients must recall as many words as possible from list A, afterwards the semantic recall follows. After 20 min, the patient is asked to recall again as many words as possible from list A, followed by a helping recall trail. For recalling, similar, semantic and phonematic distractions and categoric prototypes will be used. There are two normed settings available for baseline and t_2_.

The (sub)scores “total-trials 1–5” ascertains the learning curve for the first word list based on 5 rounds. The “short-delay” reports the delayed recall immediately after presentation and retrieval of the second word list (as interference) and without repeating the first list. The “long-delay” is testing the recall after ~20 min.

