### Sample Size Estimations and Determination of Sample Size

The following information and assumptions are used for sample size estimations:

Use of data from the study of Andreotti et al. (72) (baseline assessments in healthy women) for group A.Postulation of a 15% change of the mean scores in group A over group B for all 3 primary endpoints (Xgroup A = 1.15 ^*^ Xgroup B).Postulation of a 7.5% change of the standard deviations in group A over group B for all 3 primary endpoints (SDgroup A = 1.075 ^*^ SDgroup B).Type I error (Bonferroni-adjusted) = 0.833% one-sided.Type II error = 20%.Independent samples *t*-test.

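### Pre-tests on the trial data choose ANCOVA or Quade's test separately for each primary endpoint, and the plan does not say which values are tested for normality

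*Protocol article*

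**What the plan says.** The section on group comparisons of primary endpoints sets two gates. The first is normality: "If the hypothesis of normal distribution cannot be rejected (Kolmogorov-Smirnov with Lilliefors significance correction, type I error = 10" per cent). The second is equal variance: "if homoscedasticity exists (Levene's test; type I error = 5%) a parametric analysis of covariance (ANCOVA) will be applied". If either fails, "Otherwise, a non-parametric analysis of covariance (rank analysis of covariance according to Quade) will be used". Both branches use the 0.833% one-sided level and the same six baseline covariates: the matching CVLT score, BMI, age, BDI-II, STAI and fatigue. The section does not state whether normality is checked on raw 12-month scores (by arm or pooled) or on residuals of the ANCOVA.

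The Primary Endpoint section fixes the scale: "The test consists of two 16-word lists" and "Word list A will be read aloud to the patient 5 times". Short and long delay are therefore whole numbers from 0 to 16, and total trials 1–5 is a whole number from 0 to 80.

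The Introduction states the hypothesis in terms of mean (sub)scores, which "after 12 months of intervention are hypothesized to be higher in the intervention- than in the control group". The sample size section assumes a 15% difference in means, an independent-samples t-test, "Type I error (Bonferroni-adjusted) = 0.833% one-sided" and "Type II error = 20" per cent.

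**The concern.** The analysis that carries the confirmatory claim is picked by significance tests on the same data. A Lilliefors test on a coarse integer score can reject because of ties alone, even when the underlying trait is normal and ANCOVA with about 50 patients per arm would be sound. The pre-test may then answer a question that does not matter for the validity of ANCOVA, while still deciding which quantity is tested.

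Three things are at stake. First, the three co-ranking endpoints may be tested by different methods. Second, the per-protocol and ITT analyses of one endpoint may also differ in method, so a discrepancy between them could not be separated from the change of test. Third, Quade's test compares covariate-adjusted ranks, so it yields no adjusted difference in CVLT points to set against the mean-score hypothesis and the 15% mean difference used for sizing.

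**Working it through.** **1. The plan's own sample size.** Per-arm n = 2(z₁₋α + z₁₋β)² (SD/Δ)², with α = 0.00833 one-sided and power 80%: 2(2.394 + 0.842)² ≈ 20.94.
- Total trials: 20.94 × (7.75/7.28)² = 23.7, so 24 (plan: 25).
- Short delay: 20.94 × (2.35/1.65)² = 42.5, so 43 (plan: 44).
- Long delay: 20.94 × (2.47/1.65)² = 46.9, so 47 (plan: 48).

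The exact noncentral t gives 26/44/49. The plan's figures are reproduced to within two patients, so Table 3 is a usable basis for simulation.

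**2. How often the normality gate fails.** Inputs from the article are the Table 3 means and SDs, whole-number scores limited to 0–16 or 0–80, 48 valid cases per arm, and Lilliefors at 10%. Scores were rounded normals or, for the recall endpoints, also beta-binomial. Critical values were simulated at each n. For the residual row, a baseline correlation of 0.3 to 0.7 is assumed, because the article gives none.

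| Values tested, 48 per arm | Short/long delay rejected | Total trials rejected |
|---|---|---|
| One arm alone, raw | 75–97% | 17–18% |
| At least one arm, raw | 94–99.5% | about 32% |
| Both arms pooled, raw | 99–99.9% | 23–28% |
| Centred on group mean, no covariates | 79–97% | about 20% |
| Residuals of the six-covariate ANCOVA | 9–15% | about 9–11% |

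If both arms must pass on raw scores, and Levene's test is applied too, ANCOVA is run in about 0.1–6% of trials for the recall endpoints and about 65% for total trials. On ANCOVA residuals, 100 − 15 = 85% to 100 − 9 = 91% pass the normality gate. Levene's test rejects in about 5–6% and would take off a few points more.

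**3. Cause.** With both arms set at the group B mean, only about 2.5–3% of patients score 16, yet at least one arm is still rejected in 94–96% of trials. Coarse integer steps therefore matter more than the cap. Fitting six covariates smears the steps, which is why residuals mostly pass.

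**4. ITT set.** The article fills missing primary endpoints in the ITT set with the worst value observed in the study. With 63 per arm, 15% missing at random and the same assumed correlations, ANCOVA residuals fail Lilliefors in roughly 70–96% of trials for all three endpoints. With 5% missing they fail in roughly 37–76%. On the residual reading, the per-protocol analysis would usually use ANCOVA and the ITT analysis usually Quade's test.

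**5. Error rate and power.** Long delay, 48 per arm, two-stage rule applied to raw scores:

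| Baseline correlation (assumed) | ANCOVA | Quade | Two-stage rule |
|---|---|---|---|
| 0.3 | 78.2% | 76.9% | 76.9% |
| 0.5 | 85.7% | 84.5% | 84.6% |
| 0.7 | 96.2% | 95.5% | 95.5% |

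A separate run with 15% lost at random and correlation 0.5 gave 93.7% for ANCOVA and 91.9% for Quade. Under the null, rejection was 0.74–0.97% for all procedures against 0.833% nominal. With 4,000 to 8,000 runs the Monte Carlo standard error is √(0.00833 × 0.99167/4,000) = 0.14 points, falling to 0.10 points, so no inflation is visible.

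**The case against.** The strongest reply is that nothing here is undisclosed or invalid. Both branches are named with one alpha and one covariate list. The article also foresaw the rank branch in its sizing: the upper limit of 134 allows for a possible non-parametric test, and 126 × 0.85 and 134 × 0.80 both give about 107 valid cases against the 96 required. The formal hypotheses say only that the score is higher in group A, which a rank test can address. Arm means, SDs and medians are to be tabulated whichever test is used. The per-protocol analysis is declared paramount, so the worst-value fill-in does not touch the leading analysis. What exactly the normality test is applied to could also sit in an analysis plan that is not shown.

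Most of this stands, and it limits the point. A reader might infer that ANCOVA will almost never be run for the recall endpoints. The article does not support that, because it does not say that raw scores are tested, and on ANCOVA residuals the result reverses. A reader might also infer an inflated type I error, a serious loss of power, or a report with no effect size at all; neither the simulations nor the article's reporting section bear these out.

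What the reply does not remove is the data-driven rule itself, which the article states outright. Settling in an analysis plan which values are tested would narrow the range but would still leave the outcome data to choose the method. Tabulated arm means are not covariate-adjusted differences. The Introduction and the sizing assumptions are both about means.

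**Conclusion.** The point holds as a weakness in how the primary analysis is fixed, and not as a failure of error control. Depending on an unstated choice, ANCOVA is used for short and long delay in under 6% of trials or in about 85–90%. Two analysts following the article could report different primary analyses from the same data. On the raw-score reading, total trials would usually keep ANCOVA while the recall endpoints would not. On the residual reading, the likely split is between the per-protocol and ITT sets.

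The raw-score rates rest on Table 3 and whole-number scoring. The residual, ITT and power figures also rest on an assumed baseline correlation of 0.3–0.7, and the ITT figures on missingness at random. The cost is in the definition and estimation of the effect: the tested quantity is not settled in advance, and the rank branch has no adjusted difference in CVLT points. It should be corrected, but it does not threaten the trial's validity.

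**What to change.** In the section on group comparisons of primary endpoints:
- Delete the Lilliefors and Levene pre-tests.
- Name ANCOVA with the six listed covariates as the single confirmatory analysis for all three endpoints, in both the per-protocol and ITT sets. Heteroscedasticity-robust standard errors are an optional way to cover unequal variances.
- Report adjusted mean differences in CVLT points with intervals that match the test level: 1 − 2 × 0.00833 = 98.33% two-sided. The 95% intervals that the article plans for selected variables can stay for other purposes.
- Run Quade's test for all three endpoints as a sensitivity analysis.

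The cost is a change of wording, with no added patients and no loss of power (about 1 point gained). The drawback is slightly less robustness if ceiling effects turn out to be strong, which the Quade sensitivity analysis would show. Naming Quade's test throughout would also end the indeterminacy, but it would not supply the adjusted mean difference that the stated hypothesis calls for.

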**Patients and Methods:**

Against this background, the prospective, two-arm, 1:1 randomized, controlled trial investigates the influence of first line chemotherapy accompanied by exercise training on preventing CRCI in 126 patients with breast cancer at the local University Hospital. The study will evaluate biomarkers and secondary assessments suspected to be involved in the pathogenesis of CRCI in addition to objective (primary outcome) and subjective cognitive function. CRCI is believed to be connected to either functional and/or morphological hippocampal damage due to chemotherapy. Thus, cerebral magnetic resonance imaging (MRI) and hippocampal volume measurements are performed. Furthermore, a specific neuropsychological test battery for breast cancer patients has been developed to detect early signs of cognitive impairments in patients and to be integrated into practice.

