### Study Population and Recruitment

Patients are recruited at the department of hematology and internal oncology of the Kepler University Hospital in Linz (AUT). Patients diagnosed with local breast cancer receiving neo-/adjuvant chemotherapy and not fulfilling any exclusion criteria listed in Table 1 are advised by the attending physicians and recruited for study participation. Patients receive a detailed description of the study, can ask any question, and are included in the planned research program only after written consent, according to the ethics committee's approval. Patients can withdraw at any time and for any reason without prejudice to their medical care. Randomization procedures and randomization lists were deposited in a sealed envelope before recruitment of the first patient. Single decoding is available for each subject in sealed envelopes. The envelopes containing information about group affiliation are opened by an authorized study team member at the last possible time (at the earliest after complete baseline evaluation).

**Table 1 T1:** In- and exclusion criteria.

**Inclusion criteria**	**Exclusion criteria**
• Pending chemotherapy (neo-/adjuvant)	• Significant comorbid conditions contraindicating physical activity
• Diagnosed breast cancer	• Cognitive dysfunction, defined by subjective or diagnostic deficits in attention, memory, executive function and/or visual construction before the start of chemotherapy, as well as any known history of cognitive disorder at the baseline screening.
	• In tests without clear ranges of reference values for cognitive impairments in performance, cut-offs will be defined using >1,5 SD from normative data. Cognitive impairment therefore is defined by > 1,5 SD in two tests at baseline assessment.
• Eastern Cooperative Oncology Group (ECOG) performance status of 0 or 1	• Vigorous physical activity of >300 min weekly within the last 6 months before diagnosis of breast cancer (Evaluated by training anamnesis)
• Age ≥ 18–70 years	• Patients unwilling to complete endurance exercise or complete all questionnaires related to the study
• Adequate hematologic function Platelet count > 50 × 10^∧^9/L Hemoglobin > 8 g/dL	• Past or current history of other malignant neoplasms other than breast cancer in the last 5 years
• No motorical dysfunction leading to the disability to perform endurance exercise according to protocol	• Coronary heart disease

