• Signed informed consent prior to randomization	• Left bundle branch block
• Fluid in German	• Chemotherapy or radiation with other indications than breast cancer diagnosis
	• Current pregnancy or plans to become pregnant within the next 3 years
	• Neurodegenerative disease

All assessments are conducted at three main time points (t_0_, t_1_, t_2_) in both groups.

t_0_ (Pre): Before first chemotherapy within ± 14 days.t_1_ (interim): After 6 months ± 14 days.t_2_ (post): After 12 months ± 14 days (end of intervention).

For participants in all groups, clinical assessments during the intervention period are additionally performed at least every second month and at each clinical visit (usual care).

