### Data Collection and Timeline/Testing Procedure

Data are collected at baseline (t_0_), after 6 months of intervention (t_1_) and after 12 months of intervention (t_2_). The patient's medical record and intended therapy, demographic (age, sex) and anthropometric data (weight, height, BMI), past medical history and current medication are collected at the start. Furthermore, the primary outcome and all secondary outcome measurements of the study are captured before the first therapy session. After 6 months of intervention (t_1_), an interim exercise test is conducted to adapt the exercise workload in Arm A and in Arm B for equality. At (t_2_) the primary outcome measures and all secondary outcome measures are re-assessed. A follow-up period of 12 and 24 months is provided after the end of the intervention. The follow-up assessments therefore are parameters assessed within the clinical routine amended by the questionnaires used to assess quality of life and activity level.

A detailed study schedule is presented in Supplementary Appendix 1.

All assessments except exercise testing are performed at the Kepler University Hospital, Linz (AUT). At (t_0_), (t_1_), and (t_2_). All blood samples are drawn and stored at minus 85°C at the Kepler University Hospital Linz. Analyses of cancer-related pro- and anti-inflammatory biomarker samples are performed at the Sports University of Cologne.

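### The primary covariate list omits chemotherapy setting (neoadjuvant or adjuvant), a baseline factor already recorded; adding it is a small, optional gain in precision

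*Protocol article*

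**What the plan says.** All of the following is in the protocol article.

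- **Primary model.** The section on group comparisons of primary endpoints specifies a parametric ANCOVA, or Quade's rank ANCOVA if the distributional checks fail. It gives one closed list of six covariates for either version. The list opens with "CVLT total trials 1–5/CVLT short delay/CVLT long delay (corresponding variable) at baseline [-]BMI at baseline" and ends with "Age at baseline [years]BDI II at baseline [-]STAI at baseline [-]Fatigue at baseline [yes/no"). No term describes the chemotherapy setting.
- **Population.** Table 1 admits patients with "Pending chemotherapy (neo-/adjuvant"), so both settings are enrolled.
- **Data available.** The data collection section says that "The patient's medical record and intended therapy, demographic (age, sex) and anthropometric data" are among the items collected at the start.
- **Outcome interval.** The baseline assessment is set at "Before first chemotherapy within ± 14 days" and the final one at "After 12 months ± 14 days (end of intervention").
- **Other models.** The multiple regressions on the primary endpoints are confined to group A, so they do not adjust the between-arm contrast. Further analyses of covariance are allowed post hoc, but only descriptively.

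**The concern.** Baseline is tied to the first chemotherapy. Surgery has therefore already taken place at t0 for an adjuvant patient, while for a neoadjuvant patient it comes after t0 and normally before t2. The article does not set out this sequence; it follows from what the two terms mean. The two kinds of patient thus differ in what happens to them between the two CVLT assessments. A score taken at t0 cannot fully represent a difference that arises later.

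The trial's own rationale ties the impairment to treatment: "CRCI is believed to be connected to either functional and/or morphological hippocampal damage due to chemotherapy". A variable describing how treatment is sequenced is therefore a natural candidate for the model, and it is known before allocation. If setting is related to 12-month recall, leaving it out keeps that variation in the error term. Precision is what is at stake, not validity.

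**Working it through.** **1. The plan's own figure.** Inputs from the sample size section and Table 3 for long delay: difference 1.65 words, pooled SD 2.47, one-sided alpha 0.00833, power 80%.

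- Normal approximation: n per group = 2 × (3.236 × 2.47 / 1.65)² = 46.9, so 47.
- Noncentral t: 49 per group. At the stated 48 the power is 79.6%.

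The stated 48 is reproduced to within one patient. This calculation uses an unadjusted t-test, so it contains no covariates and the omission does not affect it.

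**2. Does leaving setting out harm the test?** Two null scenarios were simulated at 48 per group, 40,000 runs each, with simple randomisation, setting omitted and a t-test at 0.00833 one-sided.

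| Share neoadjuvant | Setting difference | Rejection rate |
|---|---|---|
| 30% | 0.5 SD | 0.0081 |
| 50% | 0.8 SD | 0.0089 |

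Both are close to nominal, so the test remains valid.

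**3. What would adjustment gain?** The documents give neither the mix of settings nor the effect of setting on the CVLT. The following are assumptions:

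- 107 evaluable patients (126 × 0.85 = 107.1);
- half of them neoadjuvant;
- baseline-outcome correlation 0.6;
- setting difference e of 0.5, 1.0 or 1.5 words on 12-month long delay, given baseline.

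Formulas:

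- Residual SD without setting = 2.47 × √(1 − 0.36) = 1.976.
- Share of residual variance due to setting, R² = 0.25 × e² / 1.976².
- Equivalent patients = 107 × (1/(1 − R²) − 1).
- Power from the noncentral t for 1.65 words, with residual SD 1.976 × √(1 − R²).

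| Setting effect e | R² | Equivalent patients | Power, 107 evaluable | Power, 48 per group |
|---|---|---|---|---|
| none in model | – | – | 96.9% | 94.9% |
| 0.5 words | 1.6% | 1.7 | 97.1% | 95.2% |
| 1.0 words | 6.4% | 7.3 | 97.8% | 96.2% |
| 1.5 words | 14.4% | 18.0 | 98.6% | 97.5% |

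The gain runs from 0.2 points (97.1 − 96.9) to 2.6 points (97.5 − 94.9). The starting power is high because the baseline CVLT score, already in the model, removes 36% of the variance under the assumed correlation.

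**4. A less favourable starting point.** Suppose no credit is given for the covariates already listed, and the share neoadjuvant is varied from 20% to 50% and the setting difference from 0.2 to 0.8 SD. Power at 48 per group then moves from 79.6% to between 79.9% and 86.9%. This overstates the gain for the planned model, because that model does include the baseline score.

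**The case against.** The strongest reply is that nothing here is an error. The plan prespecifies a baseline-adjusted analysis with sensible covariates, and a randomised comparison stays valid without any particular further one. The same complaint could be made about any other unlisted variable. This stands.

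It is also true that no section links the timing of surgery to the CVLT. Both settings receive chemotherapy after t0, so the article's attribution of impairment to chemotherapy does not by itself separate them. Where the introduction mentions treatment regimens, it is explaining why published impairment rates vary. The prognostic value of setting is therefore assumed. The largest scenario, 1.5 words, is 91% of the planned exercise effect (1.5 / 1.65).

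Three stronger readings are tempting, and the documents do not support them.

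- **That the arms will be unbalanced on setting because randomisation ignores it.** The article does not describe the randomisation scheme in detail. Stratification is commonly left to the full protocol, so silence is not evidence that it is absent.
- **That chance imbalance biases the result.** Under simple randomisation with half the patients neoadjuvant, the 95% limit of imbalance is 1.96 × √(0.25 × 4/107) = 0.19. At 1.5 words this shifts the contrast by 0.28 words. That is ordinary sampling error, inside the contrast's own 95% margin of 1.96 × 1.976 × √(4/107) = 0.75 words.
- **That the leading per-protocol analysis makes the omission serious.** Exclusions could depend on arm and setting, but the article does not say that they do. Arm-dependent exclusion is a separate matter that one covariate would not cure.

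What remains against the reply is narrow. The factor is plausible, is recorded before allocation and costs almost nothing to include. The post hoc route offers only a descriptive look at it.

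**Conclusion.** The point holds as a small improvement in precision, not as a defect. The closed list omits a baseline factor that is already collected and that the baseline CVLT score cannot fully replace. The comparison is not biased, the type I error is not inflated and the sample size figure is unaffected.

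Under the stated assumptions, adjustment would remove about 2% to 14% of residual variance and add about 0.2 to 2.6 points to power that is already near 95% or above. If setting has no relation to 12-month recall, there is nothing to gain. The conclusion rests on an assumed setting effect, an assumed even mix of settings and an assumed correlation of 0.6, none of which the documents supply.

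**What to change.** Optional. Before the allocation is unblinded for analysis and outcomes are compared by arm, add one entry to the covariate list: intended chemotherapy setting at baseline (neoadjuvant or adjuvant). Apply it to all three primary endpoints, in both the ANCOVA and the Quade version. Take the value from the intended therapy recorded at t0, not from treatment received later, so that the model does not condition on anything that happens after randomisation.

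The cost is one line in the plan and one degree of freedom. No new data are needed, and if setting proves unrelated to the CVLT the loss of precision is negligible.

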#### Secondary Endpoints

Further neuropsychological related endpoints distinguish by the variable attention and motor-speed, memory, executive functions, and visual construction.

To raise attention and psycho-motoric speed the subtest Digit Symbol Coding (of WAIS IV) is used, in which as fast as possible, symbols shall be written to different objects and the Trail Making Test A, in which numbers shall be put together in the correct order.

Memory function is captured with the subtests Logical Memory I & II (of WMS IV, memorizing texts immediately and after ~30 min). The subtest Digit Span backwards (of WAIS IV), Trail Making Test B/A (quotient of the processing times required for Trail Making Test B) and the “Regensburger-Wortflüssigkeits-Test” for word fluency (words with a special initial letter, words from a special category) measure executive functions.

At last, the subtest Block Design (of WAIS IV) in which patterns have to be recreated from a template with cubes is used to get information about the visual construction.

Secondary endpoints of physical activity and exercise related aspects are represented by performance changes obtained from exercise testing. Main variables are maximal oxygen uptake (VO_2max_) and maximal power output (P_max_), submaximal threshold values such as the first and the second ventilatory thresholds (VT_1_, VT_2_), body composition (body fat, muscle mass, Waist-to-Hip ratio, BMI) and the global physical activity questionnaire (GPAQ).

Additionally morphological changes of the heart will be objectified by strain-analyses. Speckle-tracking-echocardiography performed by Aplio-i900 (Canon) is implemented to evaluate possible chemotherapy related effects on the ventricular function.

Further patient-related endpoints like fatigue, emotional functioning/well-being, physical functioning/well-being, and QOL are measured by the Pittsburgh Sleep Quality Index (PSQI), Multidimensional fatigue inventory (MFI-20), Functional Assessment of Cancer Therapy-General (FACT-G, FACT-G/F), Beck-Depression-Inventar (BDI-II) and State-Trait-Anxiety Inventory (STAI).

Survival related endpoints are defined as the time from randomization to any signs of locoregional or metastatic recurrence or the appearance of secondary cancer or death, whichever occurs first - disease free survival (DFS) and time from randomization to death from any cause - overall survival (OS).

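### The primary model adjusts for baseline fatigue as yes/no although graded fatigue questionnaires are collected at baseline; a named score would be slightly more efficient at almost no cost

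*Protocol article*

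**What the plan says.** The Protocol article, under Group Comparisons of Primary Endpoints/Hypotheses Testing, gives one covariate list for both the parametric ANCOVA and the Quade rank analysis of covariance. It contains the matching CVLT score at baseline, BMI, age, BDI-II, STAI and fatigue. The last three read "BDI II at baseline [-]STAI at baseline [-]Fatigue at baseline [yes/no". BDI-II and STAI carry the same unit-less marker as the CVLT scores, BMI and age carry physical units, and fatigue alone is two-category ("Fatigue at baseline [yes/no"). The list serves all three equal-ranking primary endpoints.

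Under Secondary Endpoints the article says "Further patient-related endpoints like fatigue, emotional functioning/well-being, physical functioning/well-being, and QOL are measured by" a set of questionnaires that includes "Multidimensional fatigue inventory (MFI-20), Functional Assessment of Cancer Therapy-General (FACT-G, FACT-G/F". Table 2 repeats these instruments. Under Data Collection and Timeline/Testing Procedure it says that "the primary outcome and all secondary outcome measurements of the study are captured before the first therapy session", so the fatigue questionnaires are available at baseline.

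**The concern.** A covariate in the primary model earns its place by explaining outcome variance. Reducing a graded measure to two categories treats everyone on the same side of the split as equally fatigued and gives up part of that explanation. In the Quade branch a two-category covariate becomes just two tied ranks. The article gives no reason for handling fatigue differently from depression and anxiety, which are also questionnaire measures and enter unsplit.

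What is at stake is precision in the three confirmatory comparisons. A covariate measured before treatment, coded either way, does not bias a randomised comparison.

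**Working it through.** **1. The plan's own figure.** Inputs from Sample Size Estimations and Table 3: "Type I error (Bonferroni-adjusted) = 0.833% one-sided", 80% power, independent-samples t-test. For CVLT long delay, which drives the sample size, the difference is 12.62 − 10.97 = 1.65 and the pooled SD is √((2.56² + 2.38²)/2) = 2.472.

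Normal approximation: n per group = 2(z₀.₉₉₁₇ + z₀.₈)²(SD/Δ)² = 2 × (2.394 + 0.842)² × (2.472/1.65)² ≈ 47. The noncentral t gives 49. The article states 48, so the figure reproduces. It assumes no gain from any covariate, so the coding of fatigue cannot change it.

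**2. Information kept by a split.** Assume a normal score split so that a proportion p is classed as fatigued. The share of the score's explained variance that is kept is φ(c)²/(p(1 − p)), where c is the cut point and φ the normal density.

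- p = 0.5: 0.3989²/0.25 = 0.64
- p = 0.3: 0.3477²/0.21 = 0.58
- p = 0.2: 0.2800²/0.16 = 0.49
- p = 0.1: 0.1755²/0.09 = 0.34

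**3. Effect on residual variance.** Let r be the partial correlation of the fatigue score with 12-month CVLT given the other covariates. The article gives no value, so r = 0.1–0.3 is assumed. The ratio of residual variances, split to score, is (1 − r² × kept)/(1 − r²).

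- Smallest (r = 0.1, p = 0.5): (1 − 0.01 × 0.637)/0.99 = 1.0037
- Largest with p of 0.2–0.5 (r = 0.3, p = 0.2): (1 − 0.09 × 0.490)/0.91 = 1.0505

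The penalty is therefore about 0.4–5%. On the 96 valid cases (2 × 48) this is worth 0.0037 × 96 ≈ 0.4 to 0.0505 × 96 ≈ 4.8 patients.

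**4. Effect on power.** CVLT long delay, 48 per group, one-sided 0.00833, noncentral t with 94 degrees of freedom and noncentrality (1.65/SD_res) × √24. SD_res is 2.472√(1 − r²) for the score and 2.472√(1 − r² × kept) for the split. Without the covariate, power is 79.6%.

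| r | Score | Yes/no, p = 0.5 | p = 0.3 | p = 0.2 | Loss (points) |
|---|---|---|---|---|---|
| 0.1 | 80.0% | 79.9% | 79.8% | 79.8% | 0.1–0.2 |
| 0.2 | 81.4% | 80.7% | 80.6% | 80.5% | 0.7–0.9 |
| 0.3 | 83.7% | 82.2% | 81.9% | 81.6% | 1.5–2.1 |

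If only 10% were classed as fatigued, the loss at r = 0.3 would be 83.7 − 81.0 = 2.7 points. These powers treat fatigue as the only covariate. The variance ratios in step 3 do not depend on that.

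**The case against.** The strongest objection is that the article never says the yes/no variable is a split questionnaire. Past medical history is also taken at the start, and the Data Management section mentions structured interviews at baseline, so fatigue might be recorded directly as a yes/no item. That stands: the link to "Multidimensional fatigue inventory (MFI-20" is an inference, and the percentages above apply only if the binary variable stands in for such a score. It does not remove the point, because the graded measure is collected at baseline either way and could be used.

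A second objection is that the gain is small and rests on assumed inputs. This is also right. The model already adjusts for baseline CVLT, age, BMI, BDI-II and STAI, so only what fatigue adds beyond these counts, and nothing in the article points to the upper end of the range. A binary adjustment covariate is legitimate, only less efficient. A linear term for a score brings its own assumption about shape.

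Two stronger readings are tempting and are not supported.

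- A reader might infer that the plan has no definition of fatigue, so that the threshold could be picked after seeing the data. The article's only score threshold is for the cognitive tests at eligibility ("cut-offs will be defined using >1,5 SD from normative data"). But this is a condensed article, and the full protocol and SAP are not shown. Instrument and threshold are details commonly placed there, and nothing in the article says they are left open.
- A reader might infer that the trial is underpowered or the comparison biased. The 48 per group comes from an unadjusted t-test, and a baseline covariate coded either way leaves the randomised comparison and the type I error intact.

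**Conclusion.** The point holds as a minor matter of efficiency. The article fixes a two-category fatigue covariate in the model for all three primary endpoints, where graded measures are collected and the neighbouring questionnaire covariates enter unsplit. On the assumptions of a roughly normal score represented by the yes/no variable, 20–50% of patients classed as fatigued, and a partial correlation of 0.1–0.3 with 12-month CVLT, the coding gives up 36–51% of what fatigue could explain. Residual variance is then 0.4–5% larger than it need be, and power for long delay falls by about 0.1 to 2 points, still at or close to the planned 80%. No conclusion follows about validity, type I error or sample size.

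**What to change.** In the covariate list, replace the yes/no fatigue term with one baseline fatigue score as a continuous covariate, and rank it with the other covariates in the Quade analysis. Name the score exactly. The MFI-20 is multidimensional, so the text must say which total or subscale score is meant, or name the FACT fatigue score if that is preferred. Fix the choice before unblinding, in the SAP or an amendment.

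The cost is a line of text. One term replaces another, so no degree of freedom is added, and no new data, visits or patients are needed.
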